### Randomization and allocation concealment

2.3

In this study, a centralized randomization system developed by the research team randomly assigned patients to the acupuncture and sham acupuncture groups in a 1:1 ratio. The module size was set to 4, and 37 patients were randomly assigned to each group. All assignment information was unpredictable and invisible until participant inclusion, and the assignment sequences were directly notified to the acupuncturist by the system to ensure fairness of the assignment sequence hiding and randomization process. After the investigator confirms the qualified cases, a third party submits the application to the central randomization system, which automatically assigns the group information according to the randomization method and sends the group information to the investigator and acupuncturist.

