### Trial design

2.1

This study plans to conduct a single-center, investigator-blinded randomized controlled trial (RCT). By setting up the acupuncture (MA) group and sham acupuncture (SA) group for comparison, it aims to explore the efficacy and safety of acupuncture treatment for upper limb dysfunction in patients with ischemic stroke. Assessment scales related to upper limb function combined with surface electromyography (sEMG) will be used to comprehensively reflect the efficacy of acupuncture and its potential mechanisms. The study will randomly assign patients into two groups at a 1:1 ratio, with 37 cases in each group, recruiting a total of 74 patients.

The subjects will be hospitalized in the Rehabilitation Department of the Guangzhou University of Traditional Chinese Medicine Shenzhen Hospital (Futian). This study has been registered in the international traditional medicine clinical trial, and the details of the trial protocol and statistical analysis plan are available (Registration No. ITMCTR2025000228). This scheme is designed according to the SPIRIT declaration and reported according to the CONSORT 2025 as shown in Figure 1 (17). The schedule of enrolment, interventions, assessments, and visits to the participants is presented in Table 1, which also presents a schematic of the study design.

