### Blinding

2.4

The primary researchers are unaware of the patients’ group assignments. The efficacy evaluation is conducted by third-party personnel, and the database for data statistics is set up with a first-level blind, so the statisticians do not know the specific group details. Due to the limitations of acupuncture procedures, acupuncturists cannot be blinded. They are aware of the patients’ group assignments. All operations are trained in accordance with established Standard Operating Procedures (SOP). The acupuncture blinding auxiliary device was independently developed by the team and has been proven to effectively maintain blinding. According to the requirements, Type A and B blind acupuncture aids will be used in the MA and SA groups, respectively. Auxiliary device for acupuncture blind is presented in Figure 2.

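### Section 2.3 contradicts itself and the blinding statements on whether the investigator who confirms eligibility is told each allocation; if so, a single block size of 4 makes later allocations partly predictable

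*Protocol article*

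**What the plan says.** The protocol article describes the flow of allocation information in section 2.3 and the blinding in sections 2.1 and 2.4.

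- **Section 2.3, on concealment:** "All assignment information was unpredictable and invisible until participant inclusion".
- **Section 2.3, first statement on the recipient:** "the assignment sequences were directly notified to the acupuncturist by the system". The investigator is not mentioned.
- **Section 2.3, on the request:** "After the investigator confirms the qualified cases, a third party submits the application to the central randomization system".
- **Section 2.3, second statement on the recipient:** the system assigns the group and "sends the group information to the investigator and acupuncturist".
- **Section 2.3, on blocks:** "The module size was set to 4, and 37 patients were randomly assigned to each group". No other block size and no stratification factor is given.
- **Section 2.1, design label:** "single-center, investigator-blinded randomized controlled trial (RCT".
- **Section 2.4:** "The primary researchers are unaware of the patients’ group assignments". The acupuncturists are the only people described there as knowing the groups.

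The Abstract, Introduction and Discussion use a narrower label, in which the blinded person is the principal or primary investigator. Section 2.2.3 gives the investigator the decision on certain withdrawals, and section 2.8.2 has the investigator enter adverse events in the case report form.

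**The concern.** Section 2.3 gives two answers to the question of who learns the group. The second answer conflicts with the design label in 2.1 and, on its natural reading, with 2.4.

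The recipient matters because of the tasks the article gives to the investigator. In 2.3 it is the investigator who confirms that a patient qualifies, and some exclusion criteria in 2.2.2 leave room for judgement, such as the severity of spasticity, other serious primary disease, and other treatments that might affect the results. A person who makes that judgement while knowing past allocations could, knowingly or not, match patients to expected groups. The primary comparison in 2.10 is an unadjusted two-group test, so a prognostic imbalance created at enrolment would pass straight into the result. Withdrawals judged on compliance or suitability, and the recording of adverse events that 2.8.3 then compares between groups, would also be made with the group known.

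**Working it through.** **Step 1. The statements side by side**

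| Place | Who learns the group, or who does not |
|---|---|
| 2.3, earlier sentence | acupuncturist, notified directly |
| 2.3, last sentence | investigator and acupuncturist |
| 2.1 | investigator blinded |
| Abstract, Introduction, Discussion | principal or primary investigator blinded |
| 2.4 | primary researchers unaware; acupuncturists aware |

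The two rows for 2.3 disagree with each other, and the second of them disagrees with 2.1 as worded. It can be squared with 2.4 and the narrower labels only if the investigator of 2.3 is a different person from the primary researchers. The article does not say so.

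**Step 2. How far a known past predicts the next allocation**

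The article gives no figure for predictability. The inputs from 2.1 and 2.3 are block size 4, ratio 1:1 and 74 patients in total (37 + 37 = 74). The assumptions are one allocation sequence for all patients (no stratification is stated), and one screener who sees every past allocation, knows the block size and keeps track of where each block begins.

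A block of two A and two B has 6 equally likely orders. The best guess is the arm with more places left, or a coin toss when the arms are tied.

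| Position in block | Probability that it is certain in advance | Probability of a correct guess |
|---|---|---|
| 1 | 0 | 1/2 |
| 2 | 0 | 2/3 |
| 3 | 1/3 (first two alike) | 1/3 × 1 + 2/3 × 1/2 = 2/3 |
| 4 | 1 | 1 |
| Sum per block | 4/3 = 1.33 | 17/6 = 2.83 |

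The target of 74 is 18 full blocks and 2 further patients (18 × 4 + 2 = 74).

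- **Certain in advance:** 18 × 4/3 + 0 = 24 expected, and 24/74 = 32.4%.
- **Correct guesses:** 18 × 17/6 + (1/2 + 2/3) = 51 + 1.17 = 52.17 expected, and 52.17/74 = 70.5%.
- **If the screener receives no allocations:** 0 certain and 50% correct by chance.

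The range is therefore 0 to 24 certain allocations, and 50% to 70.5% correct guesses. Where a trial falls in that range depends on how many people screen and how much each of them sees.

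**Step 3. Does the block of 4 secure 37 per arm?**

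74/4 = 18.5, so the last block is half used. Its two patients fall one in each arm in 4 of the 6 orders. Blocks of 4 therefore give exactly 37:37 with probability 2/3 and do not guarantee it.

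**The case against.** The strongest reply is that this is a drafting slip or a loose use of terms. Most of the design statements concern the principal or primary investigator, and only 2.1 uses the unqualified label. The investigator of 2.3 may be a recruiting clinician outside the blinded group. The same section has a third party submit the request, keeps assignments invisible until inclusion and, in one sentence, notifies the acupuncturist alone. A reader might infer that the trial's blinding and concealment have been broken. The documents do not support that: they show conflicting instructions, not what was done, and they do not show that any bias has arisen.

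That reply softens the blinding contradiction but does not rescue concealment. Even if the recipient is not the principal investigator, section 2.3 gives the same role the confirmation of eligibility, and the third party acts only after that step.

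A second reply concerns size. A reader might take one third of allocations as known for certain in this trial. The figure is an expectation under the worst case, and it falls if several people screen and each sees only some allocations. This limit stands.

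A third reply is that other safeguards are in place. Under 2.4, third-party personnel rate efficacy and the statisticians are blinded. Under 2.10, the main analysis keeps every randomized patient who had at least one treatment and fills in missing values, with the per-protocol set used only for sensitivity. A withdrawal by the investigator does not by itself remove a treated patient. This also stands, and it limits the harm after randomization. None of it acts before randomization, where selective enrolment would occur.

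Finally, if the investigator receives no allocations, a block size of 4 is much less of a problem. What remains is leakage from the unblinded acupuncturists.

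**Conclusion.** The point holds as an internal contradiction that has to be resolved before the procedure can be followed. Section 2.3 disagrees with itself, with the label in 2.1 and, unless two kinds of investigator are meant, with 2.4. If its last sentence is followed, the person who confirms eligibility, decides withdrawals and records adverse events does so knowing the groups. The claim in 2.3 that assignments are unpredictable then fails for that person.

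The predictability in step 2 is an upper bound. It rests on one screener with full knowledge of past allocations and of the block size, and on a single sequence. The block size is already published in the article, so that part of the assumption is easily met. Whether one person screens all 74 patients is not stated. The sample size is not affected.

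**What to change.** **Main change.** In 2.3, state that the system releases the allocation only to the treating acupuncturist, and delete the investigator as a recipient. In 2.4, state that those who confirm eligibility, decide withdrawals and record adverse events are blinded, and use one term for each role throughout the article.

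**Secondary safeguard.** Against leakage from the acupuncturists, use randomly varied block sizes for the remaining allocations and do not disclose the new sizes to those who enrol. Withholding the present size of 4 would achieve little, because it is already public.

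**Cost.** The main change needs a change of recipient in a randomization system that the article says the team developed, and a short edit to 2.3 and 2.4. Varied blocks need a further system setting. The article does not make clear whether enrolment has begun. If it has, a formal amendment is needed, and allocations already disclosed cannot be withdrawn. Varied blocks may end slightly away from 37:37, which blocks of 4 do not guarantee either.

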### Blinding

2.4

The primary researchers are unaware of the patients’ group assignments. The efficacy evaluation is conducted by third-party personnel, and the database for data statistics is set up with a first-level blind, so the statisticians do not know the specific group details. Due to the limitations of acupuncture procedures, acupuncturists cannot be blinded. They are aware of the patients’ group assignments. All operations are trained in accordance with established Standard Operating Procedures (SOP). The acupuncture blinding auxiliary device was independently developed by the team and has been proven to effectively maintain blinding. According to the requirements, Type A and B blind acupuncture aids will be used in the MA and SA groups, respectively. Auxiliary device for acupuncture blind is presented in Figure 2.

**Figure 2 fig2:**
[figure not shown]
Auxiliary device for acupuncture blind. A-type device is used for MA group with openings in the center. B-type device is used for SA group with no openings. **(A)** is a diagram of the device. **(B)** is a diagram of the device in use. A refers to A-type.

### Sample size

2.5

The sample size calculation for this study was based on the primary outcome measure, the FMA-UE score. According to preliminary pilot results, the mean difference (MD) in FMA-UE scores between the acupuncture and control group after treatment was 11.5, with a standard deviation (SD) of 10.4. Meanwhile, the minimal clinically important difference (MCID) for the Chinese version of the FMA-UE is 4.6. This study was a superiority design, using PASS 15.0 software for sample size estimation. An independent samples t-test was employed, with a significance level set at *α* = 0.05 and power *β* = 0.8. It is estimated that the acupuncture group must reach the MCID value compared to the sham acupuncture group to be clinically meaningful. Therefore, the superiority margin is set equal to the MCID value of 4.6. The minimum sample size calculated is 58 cases. Considering a 20% dropout rate, the final sample size was determined to be 74 cases (37 cases each in the MA and SA groups).

### Interventions and comparison

2.6

Acupuncture treatments will be provided by licensed acupuncturists, each with at least 5 years of clinical experience, affiliated with Guangzhou University of Chinese Medicine Shenzhen Hospital (Futian). Acupuncturists will be trained in accordance with established standardized operating procedures (SOPs) to ensure uniformity of acupuncture practice. The content of communication between doctors and patients was also specified to avoid the transmission of group allocation information due to interaction.

#### Acupuncture intervention

2.6.1

According to the standardized acupuncture protocol, the MA group uses an A-type acupuncture auxiliary device with a catheter and a hollow base in the middle. Points include bilateral GV20 (Bai hui), DU14 (Da zhui), LI11 (Qu chi), PC6 (Nei guan), ST36 (Zu Sanli), and SP6 (San Yinjiao) (19). A disposable ordinary acupuncture needle (size 0.30 mm × 40 mm or 0.25 mm × 40 mm) is used for the intervention. The needle is inserted along the catheter by thrusting it along the pipe or obliquely for 10–30 mm. The participants are asked about having a sense of distress in identifying the local production of “qi.” Each acupuncture session lasts for 30 min, and the needles are inserted every 15 min, with one session per day, five sessions per week, for 4 weeks. Acupuncture point localization is based on the standards of the World Health Organization Standard Acupuncture Meridian Point Localization (published by People’s Health Press in 2010) (20). The MA group’s point selection and locations are presented in Table 2 and Figure 2 (Figure 3).

**Table 2 tab2:** The point selection and location of MA group.

Acupoints	Locations	Depth
GV20 (Bai hui)	At the head, 5 inches above the center of the hairline, or at the midpoint of the line connecting the tips of the ears	0.5–0.8
DU14 (Da zhui)	At the neck, on the posterior midline, in the infraspinal depression of the 7th cervical vertebra	0.5–1.2
LI11 (Qu chi)	At the lateral end of the elbow crease, bend the elbow and reach the midpoint of the line connecting the ulnar and lateral epicondyle of the humerus	0.5–1.2
PC6 (Nei guan)	On the palmar side of the forearm, 2 inches above the wrist crease, between the palmar longus tendon and the radial wrist flexor tendon	0.5–0.8
ST36 (Zu Sanli)	Located on the outer side of the calf, 3 inches below the calf’s nose, on the line connecting the calf’s nose and Jiexi	0.8–1.2
SP6 (SanYinjiao)	3 inches above the tip of the medial malleolus, and the posterior edge of the tibia near the bone edge depression	0.8–1.2

**Figure 3 fig3:**
[figure not shown]
Locations of the MA group.

#### Sham acupuncture intervention

2.6.2

The SA group follows standardized step-by-step instructions and operations, using a B-type acupuncture auxiliary device equipped with a catheter and a solid base in the middle, and six bilateral non-meridian points with clear localization were selected. The selection and locations of the SA group points are presented in Table 3 and Figure 4. A disposable blunt needle is passed through the plastic catheter on the base and fixed to the skin, applying a certain pressure to simulate the sensation of needling, causing a tingling sensation in the patient without penetration or inducing the sensation of getting “qi.” The treatment protocol is similar to that used in the MA group. The SA group device and operation are shown in Figure 2.

**Table 3 tab3:** The point selection and location of SA group.

Sham acupoints	Locations
SA 1	On the head, 5 inches above the hairline, 2 inches apart, and 2 inches apart from the Baihui acupoint
SA 2	At the neck, horizontally level the 7th cervical vertebrae below the spine, and open 1 inch next to the Dazhui acupoint
SA 3	At the outer end of the elbow crease, 1 inch below the Quchi acupoint
SA 4	On the palmar side of the forearm, 2 inches above the wrist crease, and 0.5 inches beside the radial side of the Neiguan acupoint
SA 5	On the outer side of the tibial crest of the calf, 3 inches under the outer knee, and 1 inch outward when the foot is 3 miles apart
SA 6	3 inches straight up from the tip of the medial malleolus, 0.5 inches forward from the Sanyinjiao acupoint on the tibia

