#### Other outcomes

2.7.3

sEMG is a technique for recording the bioelectrical signals of the neuromuscular system during muscle activity (13), which can quantify muscle functional status. It was recorded using a 10-channel multi-lead 060525001 Myotrac3 surface electromyograph (THOUGHT, Canada). The evoked potentials of the core upper limb muscle groups (including pectoralis major, deltoid, biceps brachii, triceps brachii, brachioradialis, etc.) defined by neuroanatomy experts were collected. The specific indicators include the root-mean-square value (RMS) and integrated electromyography value (iEMG) of the time-domain indicators, which quantify the overall muscle activation strength from the perspectives of transient intensity and cumulative loading, respectively. Frequency domain indicators include the median frequency (MF), defined as the frequency point corresponding to 50% of the energy accumulation in the spectrum, to infer muscle fiber conduction velocity (MFCV), which is used to assess muscle fatigue (28). Before collection, evaluators need to undergo standardized training to regulate the movement patterns of the core muscle groups; then the evaluators guide the patients in exercise to practice and master the standardized movement methods; secondly, before collection, the signal acquisition parameters of the instrument need to be pre-tested to ensure parameter stability. The specific operation is as follows: Inform the patient before the test to perform relevant actions according to sEMG. The patient is in a sitting position before applying the electrode sheet, local hair removal is carried out on the site where the electrode sheet is to be applied, the skin surface is polished with a special sanding pad, and then wiped with an ethanol cotton ball to remove the skin cuticle, reduce the contact resistance between the electrode and the detection surface, and protect the electrode to avoid movement and avoid errors as much as possible. After completing the electrode affixing, the electromyographic signal becomes stable, and detection begins. According to the machine’s instructions, the doctor and patient cooperate to complete the corresponding active and passive movements. Each movement lasts for 15 s, followed by a 5-s rest. Each movement is repeated 3 times as one set, with a 1-min rest after each set. The middle 10 s of the electromyographic signal for each movement is used for analysis.

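### Only the real needles break the skin of the rated arm, so skin marks could reveal the group to the scale raters at weeks 2 and 4, and to the sEMG therapist at week 4

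*Protocol article*

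**What the plan says.** **Real acupuncture (2.6.1).** The points include LI11 at the elbow crease and PC6 on the palmar forearm, both bilateral, so the affected arm is needled. Needles are 0.25 or 0.30 mm in diameter. "The needle is inserted along the catheter by thrusting it along the pipe or obliquely for 10–30 mm". Treatment is given "with one session per day, five sessions per week, for 4 weeks".

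**Sham (2.6.2, Figure 2, Table 3).** "B-type device is used for SA group with no openings". A blunt needle is pressed on the skin, "causing a tingling sensation in the patient without penetration or inducing the sensation of getting" qi. On the arm it is applied at SA 3, 1 inch from LI11, and SA 4, 0.5 inch from PC6.

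**Assessments (Table 1, 2.7).** FMA-UE, ARAT and MSS are rated at baseline, weeks 2 and 4, and 3 months. sEMG is recorded at baseline and week 4 only.

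**Masking (2.4, 2.6, 2.7.4).** The article describes a device that conceals the act of needling, SOP training and controlled communication with patients. For the raters it says "The efficacy evaluation is conducted by third-party personnel". The blinding index uses participants' guesses only.

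**sEMG preparation (2.7.3).** "local hair removal is carried out on the site where the electrode sheet is to be applied", after which the skin is abraded and wiped. Brachioradialis is among the muscles recorded.

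**The concern.** The masking measures deal with what the participant sees and feels during needling, and with who is told the allocation. A mark left on the skin is a different route. It needs nobody to disclose anything, and it can differ between groups on the very limb that the rater watches through the elbow, forearm, wrist and hand items.

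The primary outcome is scored by a rater, and the Discussion itself names evaluator subjectivity as a source of bias in such scales. A lean caused by recognising the group would probably run in one direction and could not be removed in the analysis. It would also go unseen, because no rater guess is collected. Excluding nonspecific effects is a stated aim of the trial (Introduction), so the blinding of the rated scale carries much of its argument.

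**Working it through.** **1. The plan's own figure.** Section 2.5 gives an expected difference of 11.5, SD 10.4, margin 4.6, alpha 0.05 and power 0.80.

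- n per arm = 2 × (1.645 + 0.842)² × 10.4² / (11.5 − 4.6)² = 28.1, rounded up to 29, so 58 in total.
- With 20% dropout, 29 / 0.8 = 36.25, rounded up to 37 per arm, so 74.

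The stated 58 and 74 reproduce with a one-sided 5% level. The present point does not depend on them. They only fix the SD and group sizes used below.

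**2. Exposure of the rated arm.** Two points (LI11 and PC6) lie on the affected arm. I count one insertion per point per session and full attendance.

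| | Sessions so far | Acupuncture, affected arm | Sham, affected arm |
|---|---|---|---|
| Week 2 | 5 × 2 = 10 | 2 × 10 = 20 | 0 |
| Week 4 | 5 × 4 = 20 | 2 × 20 = 40 | 0 |

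These are cumulative punctures, not marks visible on the day.

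**3. Which assessments are exposed (Table 1).**

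- Week 2: FMA-UE, ARAT and MSS. There is no sEMG at this visit.
- Week 4: the same scales, and sEMG.
- 3 months: the scales, long after the last session.

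**4. What a rater lean would do.** The documents give no size, so 1 and 2 FMA-UE points are assumed, as a shift of the whole mean difference towards acupuncture. The true difference is 0, the SD is 10.4, and the test is a two-sided 5% t-test of no difference, the form of comparison in section 2.10.

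- Standard error = SD × √(2/n). For n = 37: 10.4 × √(2/37) = 2.42. For n = 29: 10.4 × √(2/29) = 2.73.
- Noncentrality = lean / standard error. For n = 37: 0.41 and 0.83. For n = 29: 0.37 and 0.73.
- The rejection rate comes from the noncentral t distribution with 2n − 2 degrees of freedom.

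| Assumed lean | 37 per arm | 29 per arm |
|---|---|---|
| 0 | 5.0% | 5.0% |
| 1 point | 6.9% | 6.5% |
| 2 points | 12.9% | 11.1% |

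**The case against.** Four objections carry weight.

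- **Recognisable marks are inferred.** The needles are fine, the interval between a session and a rating is not given, and a pressed blunt needle may leave its own mark close by. A rater would have to tell a puncture from a pressure mark or know both sets of points. This stands, and it limits the point to a risk. A reader might infer that raters are in fact unblinded, but nothing in the article shows that.
- **A condensed article may leave the care of needle sites to the SOPs or the full protocol.** This also stands: silence here does not prove that no covering is planned. The point rests instead on the stated contrast between a penetrating and a non-penetrating needle on the rated limb, and on the fact that none of the masking measures described reaches it.
- **sEMG is a weaker case.** It is recorded by a separate therapist, yields instrument values, and its skin preparation applies to both groups. What that therapist sees does not by itself unblind the FMA-UE rater. A reader might extend the concern to sEMG at week 2, but none is scheduled then.
- **The size is assumed.** A reader might count 80 punctures, but that adds both arms; the affected arm has at most 40. A reader might also test against the 4.6-point margin, one-sided at 5%, where the same leans give 10.8% and 20.5% at a true difference of 4.6. Section 2.10 describes an ordinary comparison of groups without a margin, so those figures do not describe the planned analysis.

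**Conclusion.** The point holds as a preventable risk to rater blinding. It applies to the scales at weeks 2 and 4, and to sEMG at week 4 only. Up to 40 punctures on the affected arm against none is a real asymmetry in the stated design. Whether it is visible, and whether raters would act on it, the document does not say.

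A lean of 1–2 points would raise the false-positive rate of the two-sided 5% test from 5% to about 7–13% with 37 per arm. That range rests wholly on the assumed lean, on its affecting the mean of every rating, and on all 74 participants being analysed; with 29 per arm it is 6.5–11.1%. The article gives no ground for extending the concern to the 3-month rating.

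The case for acting is that the protection costs little and a rating made unblinded cannot be repaired later.

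**What to change.** Add to sections 2.4 and 2.6:

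- Before each week 2 and week 4 scale rating, a member of staff who does not rate (for example the acupuncturist, who already knows the group) covers the LI11/PC6 and SA 3/SA 4 areas with identical opaque patches, in the same way in both groups.
- Where a treatment session falls on a rating day, the rating comes first.
- At week 4 the scales are rated before sEMG. Standard electrode positions are kept, and any patch that would displace an electrode is removed or trimmed only after the scales are done.

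Optionally, record each rater's guess of the group at weeks 2 and 4, so that rater blinding can be checked as participant blinding already is.

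The cost is adhesive patches, a few minutes per visit and a short SOP paragraph. The analysis and sample size do not change. Some exposure of the sEMG therapist at week 4 remains, which is preferable to moving electrodes. If the SOPs already cover the sites, one sentence in section 2.4 saying so is enough.
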